
## Methods

### Design

The study is designed as a prospective, monocentric, parallel-group, feasibility RCT with subsequent intervention. A total of 128 clients of group-based SCs in VR-seminars will be randomized to either the intervention group (IG, *n* = 64) or wait-list group (WLG, *n* = 64). Each study facilitator will conduct four SC-VR seminars in tandem-partnership. The short-term intervention outcome will be measured including three assessment points: baseline and 2-week and 4-month follow-up, with the latter representing the primary endpoint. In addition, we will assess mid-term effects at 8-month follow-up and long-term effects at 12-month follow-up.

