##### Estimation of effect sizes

RQ3.1: The potential effect of SCs in VR to relate to the SCs versus the VR environment will be questioned in semi-structured experience-based interviews [35].RQ3.2: The estimation of effect sizes and 95% CI for change will concentrate on the proposed secondary outcome, i.e., psychological functioning (OQ-45.2), from baseline to 4-month follow-up.RQ3.3: In addition, effect sizes and 95% CI for change in the proposed secondary outcomes, i.e., systemic functioning (EXIS), psychological distress (FEP-2), motivational incongruence (INK-SF), and goal attainment (GAS), will be calculated from baseline to 4-month follow-up.RQ3.4: The proportion of clients experiencing clinically meaningful change, i.e., remission, response, deterioration, and no change, will be explored for the proposed secondary outcome (OQ-45.2)

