For *estimation of effect sizes*, we will use QCA and/or CQR to analyze information about the association of these effects to either the SCs or the VR environment, or both (RQ3.1). Because clients within groups (i.e., SC-VR seminar) may be more similar to each other than clients in different SC-VR seminars, a two-level linear regression analysis will be performed to account for potential clustering effects at higher levels (i.e., clients nested within SC-VR seminars). The intraclass correlation (ICC) coefficient from the random intercept model with clients (level 1) and SC-VR seminar (level 2) will be calculated for the proposed secondary outcome (OQ-45.2) [46]. An ICC greater than zero will indicate a clustering effect, and any statistical analysis must be adjusted for this effect. All proposed outcomes will be analyzed as intention-to-treat using mean scores (M), standard deviations (SD), and 95% CI. Missing values of less than 20% will be replaced with the conditional mean value of the four subgroups (ACs in IG, and WLG; OCs in IG, and WLG). This will be compared to per-protocol analyses. We then will use mixed-design ANOVAs (group: IG, WLG; client status: AC, OC; time: baseline, 2-week and 4-month follow-up), adjusting for baseline scores considering demography as well as outcome data. Because treatment outcome will be measured at three assessment points, within-group effects will be further analyzed by comparisons between baseline and 2-week follow-up (contrast A), and by comparisons between 2-week and 4-month follow-ups (contrast B). Effect sizes will be presented as partial eta-squared values (η^2^) and Cohen’s *d*, calculated as the difference between the means divided by the pooled standard deviation $$(d=\frac{{x}_{1}^{2}-{x}_{1}^{2}}{\frac{\sqrt{{s}_{1}^{2}+{s}_{2}^{2}}}{2}})$$. Classification of *effect sizes* will be as follows: η^2^ ≥ 0.010, small effect; η^2^ ≥ 0.060, medium effect; η^2^ ≥ 0.140, large effect; Cohen’s *d* ≥ 0.20, small effect; *d* ≥ 0.50, medium effect; and *d* ≥ 0.80, large effect [47] (RQ3.2, RQ3.3). The exploration of *reliably significant change*, i.e., the proportion of remission, response, deterioration, and no change, will be limited to the proposed secondary outcome (OQ-45.2) based on the reliable change index (RCI) [48]. We will use previously established internal consistency reliabilities to calculate the RCI [49] and Jacobson and Truax’s [48] cutoff C for the categorization of the clients’ (no) change [26–28] (RQ3.4).

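### Adjustment of all five outcomes for seminar clustering hinges on the sign of one OQ-45.2 ICC estimate, and the ANOVAs that follow have no seminar term

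*Protocol article*

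**What the plan says.** All of the text at issue is in the paragraph on estimating effect sizes in the Analysis section of the protocol article.

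- It recognises that clients in the same seminar may resemble each other and states, without a condition, that "a two-level linear regression analysis will be performed to account for potential clustering effects at higher levels".
- The ICC from the random-intercept model "will be calculated for the proposed secondary outcome (OQ-45.2"). No ICC is planned for the other four outcomes.
- The rule follows: "An ICC greater than zero will indicate a clustering effect, and any statistical analysis must be adjusted for this effect".
- The outcome analysis is then named: "We then will use mixed-design ANOVAs (group: IG, WLG; client status: AC, OC; time: baseline, 2-week and 4-month follow-up"). No seminar factor or random effect appears in that list.

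The Estimation of effect sizes section asks for effect sizes with 95% CIs for OQ-45.2 and also for "systemic functioning (EXIS), psychological distress (FEP-2), motivational incongruence (INK-SF), and goal attainment (GAS), will be calculated from baseline to 4-month follow-up". Aims and objectives (RQ3.2, RQ3.3) describes these as within-subjects effect sizes.

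On the layout, the Design section says "A total of 128 clients of group-based SCs in VR-seminars will be randomized", 64 per arm, and "Each study facilitator will conduct four SC-VR seminars in tandem-partnership". Biases and limitations gives four facilitators. The abstract says that the wait-list group is treated after 4 months.

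**The concern.** Clustering follows from the design: clients are treated together in groups, and the article itself expects similarity within a seminar. Whether to allow for it should not turn on a noisy estimate. With few seminars, the sign of an ICC estimate is uncertain, and the sign for OQ-45.2 need not match the clustering of EXIS, FEP-2, INK-SF or goal attainment.

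The second problem is internal. Adjustment is called mandatory once the switch fires, but the model named next has nowhere to put it, and the article does not say how the two-level regression and the ANOVAs relate.

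At stake are the 95% CIs around the effect sizes. If clustering is ignored they are too narrow, and these estimates are meant to inform the size of the confirmatory trial.

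**Working it through.** **The plan's own figures.** The article gives no ICC and no seminar count. Its sample sizes reproduce: 2 × (1.960 + 0.842)² / 0.3² = 174.4, so 175 per arm and 350 in total; 4 × (0.842 / 0.3)² = 31.5, so 32 for the pilot. Both use individual-level variance without clustering. The point does not depend on them.

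**Inputs.**
- 64 clients per arm (Design).
- Four facilitators with four seminars each. If tandem means two facilitators per seminar, 4 × 4 / 2 = 8 seminars, presumably four of 16 in the intervention group. If not, up to 16 seminars, or eight of 8. Both layouts are assumptions.
- Wait-list clients are untreated up to 4 months, so they are taken as unclustered.
- True ICC of the analysed quantity: assumed 0 to 0.10.

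**Step 1: chance that the switch does not fire.** With k intervention-group seminars of size m, the ANOVA estimate of the ICC is zero or below when the between/within F ratio is at most 1:

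P = P( F(k−1, k(m−1)) < 1 / (1 + m × ICC / (1 − ICC)) )

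**Step 2: coverage of an unadjusted 95% CI.** With design effect DE = 1 + (m − 1) × ICC:
- within the intervention group: 2Φ(1.96 / √DE) − 1
- between groups, wait-list unclustered: 2Φ(1.96 / √((DE + 1) / 2)) − 1

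At ICC 0.05 and m = 16, DE = 1.75. Within: 1.96 / 1.323 = 1.48, coverage 86%. Between: 1.96 / √1.375 = 1.67, coverage 90.5%. At m = 8, DE = 1.35, giving 91% and 93%.

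| True ICC | Estimate ≤ 0: 4×16 / 8×8 | Between-group coverage, unadjusted | Within-group coverage, unadjusted |
|---|---|---|---|
| 0 | 60% / 56% | 95% / 95% | 95% / 95% |
| 0.02 | 48% / 46% | 93% / 94% | 91% / 93% |
| 0.05 | 35% / 33% | 91% / 93% | 86% / 91% |
| 0.10 | 22% / 19% | 86% / 91% | 78% / 87% |

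Simulation of 40,000 trials agrees with the coverage columns to within about half a percentage point. Always adjusting gives about 94% between-group coverage with four seminars of 16 and 95% with eight of 8.

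**Step 3: coverage under the rule as written.** Take another outcome that also has ICC 0.05, with the OQ-45.2 estimate independent of it.
- Between groups, 4×16: 0.345 × 0.905 + 0.655 × 0.942 = 0.929.
- Between groups, 8×8: 0.331 × 0.929 + 0.669 × 0.950 = 0.943.
- Within the intervention group, taking adjusted coverage as 0.95: 0.345 × 0.86 + 0.655 × 0.95 = 0.919 (4×16) and 0.331 × 0.908 + 0.669 × 0.95 = 0.936 (8×8).

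If the two outcomes correlate 0.7 at both levels (assumed), between-group coverage for 4×16 is about 94.4%; for 8×8 simulation gives up to about 95%.

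**Step 4: sensitivity.** If the ICC is estimated over the seminars of both arms while only the intervention group is clustered, the estimate is zero or below in about 36% of trials at ICC 0.05. If both arms are clustered, it is about 22-23%.

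**Step 5: the ANOVA.** This needs no arithmetic. One sentence requires any analysis to be adjusted; the factor list of the analysis that follows has no seminar term.

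**The case against.** The strongest reply is that the plan does not ignore clustering. The two-level regression is announced without a condition, and the adjustment sentence covers any analysis. The bracket after the ANOVAs lists design factors and does not expressly exclude seminar, and how the seminar effect enters may be set out in a fuller document. This stands in part: the article should be credited with the two-level model. It does not remove the problem, because the article itself fixes the sign rule and ties the ICC to one outcome. That is a stated choice, not missing detail.

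A reader might infer that the rule adjusts OQ-45.2 and leaves the other four outcomes unadjusted. The text does not support this: a positive estimate triggers adjustment of all five, and an estimate of zero or below leaves all five unadjusted.

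A reader might also arrive at a larger harm. If OQ-45.2 had no clustering and EXIS had ICC 0.10, between-group coverage for EXIS would be 0.60 × 0.860 + 0.40 × 0.940 = 0.892. That needs an extreme pair of ICCs and four intervention-group seminars; with eight it is 92.8%. Nor is it shown that OQ-45.2 says nothing about EXIS, since OQ-45.2 also scores interpersonal relations and social role performance.

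Further, between-group coverage is not the quantity named in RQ3.2 and RQ3.3, which are within-subjects. The within-group figures above are closer, and they are less favourable to an unadjusted analysis.

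Finally, a switch based on each outcome's own ICC would keep overall between-group coverage acceptable (0.953 at ICC 0.05, four seminars). A smaller edit would therefore cure part of the problem, but it would still leave the ANOVA without a seminar term.

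**Conclusion.** The point holds in a limited form. Adjustment of all five outcomes depends on whether one OQ-45.2 ICC point estimate exceeds zero, and the ANOVAs named afterwards offer no seminar term. At an assumed ICC of 0.05, the switch fails to fire in about a third of trials. An unadjusted interval then covers about 91-93% between groups and 86-91% within the intervention group. Under the rule as a whole the loss is smaller: about 93-95% between groups when both outcomes have that ICC, and about 92-94% within the intervention group.

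These sizes rest on an assumed seminar count (four or eight in the intervention group), an assumed ICC and an unclustered wait-list group. The mismatch between the adjustment sentence and the ANOVA factor list rests on none of them. Biases and limitations calls all analyses descriptive and explorative, so severity is moderate to low. It is still worth correcting because the intervals and the ICC feed the planning of the confirmatory trial. If both arms there were clustered at ICC 0.05 in seminars of 16, 350 clients would become 350 × 1.75 ≈ 613.

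**What to change.** - Delete the rule that an ICC above zero decides whether to adjust.
- For each outcome, use the announced mixed model in place of the plain ANOVA. Include a client effect and a seminar effect for treated clients, with Satterthwaite or Kenward-Roger degrees of freedom, whatever the ICC estimate turns out to be. Derive the effect sizes and their 95% CIs from that model.
- Report the ICC of every outcome with its CI as a planning quantity for the confirmatory trial, not as a switch.
- State the planned number of seminars per arm.

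The cost is analysis wording only; no data collection changes. The downside is wider intervals: at ICC 0.05 the median between-group half-width rises from about 0.35 SD to about 0.44 SD with four intervention-group seminars, or 0.39 SD with eight.

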**Discussion:**

The study is expected to be the first study on the feasibility of SC-VR. We will reflect on successfully implemented study procedures, and we will provide recommendations for changes considering the design, rationale, analyses, and interpretation of the study results where they became necessary. The discussion will conclude with an evaluation whether a confirmatory RCT on SC-VR is worth the investment of future resources, including the calculated number of clients needed based on the efficacy trends derived from this feasibility study.

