### Sample size calculation

Although feasibility studies, e.g., to develop an intervention, do not require a sample size calculation, it was important for us to ground the number of participants in our study on a statistical rationale that would allow a statement to be made about the sample size needed for a confirmatory trial. Cocks and Torgerson [31] used a confidence interval (CI) approach to calculate pilot sample sizes for continuous outcome measures. Supposed 0.3 of a standard deviation between two groups would be worthwhile, then such a study requires about 350 clients (assuming 80% power, two-sided alpha of 5%) in the final analysis of the fully powered RCT. Consequently, 32 clients (approximately 9% of the main sample size) would be required to produce a one-sided 80% confidence limit. A pilot trial with that sample size which finds an estimate larger than zero is supposed to demonstrate feasibility of a confirmatory RCT considering the recruitment and retainment of clients and so forth. According to this approach for two-arm feasibility RCTs, we will recruit a minimum of 32 clients. Since we are in the good position of sufficient personal and financial resources, we can include more clients in our study, and if possible, we will recruit 128 individuals, i.e., 64 clients in the IG and WLG, respectively (Fig. 1).

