### Randomization

Following inclusion, clients will be randomized using restricted randomization to obtain a balanced sample size between groups for each seminar. Therefore, we will use a randomization plan generator (www.randomization.com). The random allocation rule will be implemented according to the restricted shuffled approach, a kind of block randomization which we will perform in a 1:1 ratio [34]: every 2 people will be statistically paired and randomly assigned to either the IG (*n* = 64) or WLG (*n* = 64), after stratification by role, i.e., voluntary choice to participate either as an AC or OC prior to randomization. The randomization procedure will be performed by an independent researcher who is not involved in the study.

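### The printed formula for Cohen's d contradicts its own verbal definition: its numerator is zero and its denominator is not the pooled SD

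*Protocol article*

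**What the plan says.** In the protocol article, Methods, Analysis (the paragraph on estimation of effect sizes), Cohen's d is "calculated as the difference between the means divided by the pooled standard deviation". The formula in brackets straight after these words reads, in plain notation:

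d = (x1² − x1²) / ( √(s1² + s2²) / 2 ).

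The same paragraph then labels d as small, medium or large from 0.20, 0.50 and 0.80, and ties these effect sizes to RQ3.2 and RQ3.3.

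The observed effects have a planned use. The Discussion paragraph of the Abstract says that the report will include "the calculated number of clients needed based on the efficacy trends derived from this feasibility study", and Aims and objectives also links the effects seen here to the size of a later trial.

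Sample size calculation is separate from this. It starts from an assumed difference ("Supposed 0.3 of a standard deviation between two groups would be worthwhile"), states that such a trial "requires about 350 clients (assuming 80% power, two-sided alpha of 5"%), and derives a pilot minimum: "32 clients (approximately 9% of the main sample size) would be required to produce a one-sided 80% confidence limit".

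**The concern.** Words and symbols in one sentence give different answers, and this is the only effect-size formula in the document. It has two separate faults.

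- **Numerator.** The same squared symbol appears on both sides of the minus sign. There is no second mean, and the difference is zero for any data.
- **Denominator.** The root closes before the division by 2. For two groups of equal size, the pooled SD has the 2 inside the root.

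The first fault cannot go unnoticed, because it yields nothing usable. The second can: once the numerator has been put right, the denominator gives plausible values on the wrong scale. Estimating effect sizes is one of the three stated aims, and required sample size varies with 1/d², so an error of scale in d would carry into the plan for the confirmatory trial.

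**Working it through.** **1. The plan's own figures.** The inputs are from Sample size calculation: difference 0.3 SD, two-sided alpha 5%, power 80%. Two equal arms are assumed for the later trial, in line with the 1:1 ratio under Randomization.

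- Per arm: n = 2 × (1.960 + 0.842)² / 0.3² = 174.4, rounded up to 175. The total is 350, as stated.
- Pilot: N = 4 × (0.842 / 0.3)² = 31.5, rounded up to 32, as stated (32/350 = 9.1%).

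Both figures reproduce from the assumed 0.3 SD without the printed formula.

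**2. The formula read literally.** x1² − x1² = 0, so d = 0 in every data set.

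**3. Numerator repaired, denominator as printed.** The ratio of the correct to the printed denominator is

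√((s1² + s2²)/2) ÷ (√(s1² + s2²)/2) = 2/√2 = √2 = 1.414,

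whatever the two SDs are. For example:

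- SDs 20 and 20: correct 20.00, printed 14.14, ratio 1.414.
- SDs 15 and 25: correct 20.62, printed 14.58, ratio 1.414.

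With unequal groups and the df-weighted pooled SD, the factor moves slightly. With illustrative sizes of 60 and 50 and SDs of 15 and 25, it is 1.383.

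**4. Effect on the labels.** A d on the printed scale of 0.20, 0.50 or 0.80 corresponds to a true d of 0.20/1.414 = 0.14, 0.50/1.414 = 0.35 and 0.80/1.414 = 0.57.

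**5. Effect on a later sample size.** The table uses the same normal approximation as step 1, for a two-group comparison. Power is at the true d, with the N that the inflated d would suggest.

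| True d | d reported | Total N needed | Total N from reported d | True power |
|---|---|---|---|---|
| 0.20 | 0.283 | 786 | 394 | 51.0% |
| 0.30 | 0.424 | 350 | 176 | 51.2% |
| 0.45 | 0.636 | 156 | 78 | 51.1% |
| 0.50 | 0.707 | 126 | 64 | 51.6% |
| 0.80 | 1.131 | 50 | 26 | 53.2% |

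A t-based calculation at d = 0.424 gives 89 per arm (178 in total) in place of 88 (176). The difference is one of method only.

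**The case against.** The strongest reply is that the sentence already settles the matter. Its words are right and the formula as printed cannot be used, so anyone computing d must go back to the words, and these fix the denominator as well as the numerator. Inflation needs an analyst who takes the numerator from the words and the denominator from the misprint. Nothing in the document shows that this will happen. That part of the reply stands, and it makes the inflation conditional.

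Other parts of the reply also hold:

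- The zero numerator and the 1.41 inflation cannot both apply. They belong to different readings of the formula.
- The criterion in Sample size calculation is whether the pilot estimate exceeds zero. Multiplying an estimate by a positive constant does not change its sign.
- Effect sizes are the third of three aims and concern secondary outcomes. Means, SDs, confidence intervals and partial eta-squared are also planned, so a reader of the results could recompute d and detect the error.
- RQ3.2 and RQ3.3 ask for within-subjects effect sizes, whereas step 5 of the working is a two-group calculation. The factor √2 follows from the formula for any pair of SDs, but the sample sizes only illustrate what it would do to a two-arm trial.

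Damage from text extraction cannot be fully excluded. It is unlikely, because the formula survives as well-formed markup with a closed root over a separate 2.

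The reply does not remove the contradiction. A prespecified formula that disagrees with its own definition should be corrected, and the fault in the denominator is the kind that can pass unnoticed.

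**Conclusion.** The point holds as an internal contradiction with a conditional consequence. Read literally, the formula gives d = 0. With only the numerator repaired, d is 41% too large when the groups are of equal size. A confirmatory trial sized on that d would then have about half the clients that it needs and a true power of about 51% to 53% over true effects from 0.20 to 0.80. For a true d of 0.30, the total would be about 176 to 178 instead of about 350. These sample sizes assume two equal arms, two-sided 5% alpha, 80% planned power and a later calculation that takes the reported d at face value.

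A reader might infer that the plan will inflate its effect sizes, or that its sample size is wrong. The document supports neither. The verbal definition is correct, no analysis code is shown, and 350 and 32 reproduce from the assumed 0.3 SD without this formula.

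**What to change.** Replace the printed formula with one that agrees with the sentence:

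d = (mean1 − mean2) / √((s1² + s2²)/2),

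or, where group sizes differ, use the df-weighted pooled SD, √(((n1 − 1)s1² + (n2 − 1)s2²)/(n1 + n2 − 2)), as the denominator.

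Confirm that the analysis code computes d in this way before any value of d informs the confirmatory sample size. The correction needs no further choice of which SDs to use, since the sentence already specifies the pooled SD.

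The cost is one line of text and one check of the code. No design feature, stated sample size or collected data item changes.

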## Discussion

To the best of our knowledge, this will be the first study to explore the feasibility of SCs in VR in a prospective, monocentric, parallel-group, feasibility RCT with subsequent intervention. The challenge is to apply SC in VR as this technology has not yet reached the mainstream, so facilitators and clients must be familiarized with this innovative environment.

### Innovative aspects

What most formats of SCs have in common is that they require a group setting in the presence with 10 or more clients. Therefore, the intervention usually takes place within 1- to 3-day SC seminars. This requires greater logistical, time, and economic investments, which makes it difficult to use SCs regularly in everyday counseling. The in-person setting also increases the barrier for people who want to work on their personal issue, i.e., chronic psychosocial conflicts, as anonymously as possible. A new, expanded and possibly lower-threshold approach might be the participation in a SC in VR.

